## Methods

### Design

To facilitate transparency, the current protocol paper was written in accordance with the SPIRIT guidelines [42]. The SPIRIT Checklist is provided in the Supplemental Material.

This study is a multicenter, parallel groups, randomized controlled trial of the PRIMARY intervention compared with a waiting list control in outpatients aged 12 to 25 years (inclusive). The study also includes a nested evaluation of the effect of PRIMARY on the effectiveness of subsequent specialized treatment (HYPE) [41].

The design of the PRIMARY study was co-created by clinicians, young people with lived experience of mental ill-health, and researchers to ensure it is acceptable to all. For example, young people with lived experience provided feedback on how to adapt the ESM lay-out and script for the weekly report sessions to appeal to their age group. To guarantee the intervention is easy-to-implement, it is constructed to be delivered by research assistants (RA’s) rather than clinicians. RA’s hold a bachelor’s diploma in psychology or a related field and completed a suicide prevention e-learning module. Adherence to the prescribed PRIMARY intervention is promoted via detailed study procedures and scripts, as well as routine joint appointments with the RA, participant and AA or [name]. All individual participant data (i.e., questionnaires and weekly, graphical reports) are made available within the electronic patient record of the participant. This is a direct benefit of participation in the study for the participant, as this information can be integrated into their diagnostic or treatment process by their clinician.

### Sample and setting

Young people aged 12 to 25 years (inclusive), with varying psychological problems, will be recruited after referral to one of the two participating mental healthcare institutions in the Netherlands: GGz Centraal and Mondriaan. These young people are awaiting further care at the institutions. Study inclusion criteria are: (1) engagement in at least one act of self-harm in the past year, and (2) sufficient understanding and skills in the Dutch language. In order to reflect ‘real world’ clinical practice, there are no exclusion criteria regarding participation in the study; participants can receive other interventions if judged necessary by the clinician in charge, also during participation in the study.

### Recruitment procedure

Figure 1 depicts a flow diagram of the study design. A feasibility study was conducted to ensure an optimal design and recruitment procedure. Adjustments were made based on interviews with the participants. A description of the feasibility study can be found in the Supplemental Material. In this paper, the finalized procedures are described.

**Fig. 1 Fig1:**
[figure not shown]
Flow diagram of the study design

Young people receive an information letter about the PRIMARY study from the clinician or RA during their first formal contact at the mental healthcare institution (e.g., screening or intake session). After a two-day consideration period, an RA contacts the young person to further discuss participation and answer any questions. If the young person chooses to participate, written informed consent is obtained (also from parents or legal guardians for those aged < 16 years). A copy of the consent form is included in the Supplemental Material. Next, the young person fills out a brief screening questionnaire to confirm eligibility for the trial. If inclusion criteria are met, the baseline assessment (Wave 1) is scheduled with the RA, after which the young person is randomly assigned to a study group. At the end of the baseline assessment, the participant, independent of study group, can choose between two selected charities for the study to donate €5,00 to for their participation.

### Randomization and group allocation

Once eligibility is confirmed during screening, participants are randomly assigned to the intervention or the comparison group in a 1:1 ratio by an independent researcher using computer-generated randomization sequences with stratified block randomization by age (12 to 15 years / 16 to 25 years). Staff will not be blind to group allocation. Participants are blind to their allocated group during Wave 1 assessment. The nature of the intervention precludes concealment from participants and staff. Recruitment and retention in the trial will be maximized via study-specific training of RA’s and weekly staff-meetings to discuss the progress of the trial. In addition, retention was considered in great detail when designing the study by integrating input from young people with lived experience with mental-ill health, conducting a feasibility study and integrating recommended adjustments to increase compliance, and implementing insights from earlier ESM-studies.

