**Methods:**

This study is a multicenter, parallel groups, randomized controlled trial (RCT) comparing the PRIMARY intervention to a waiting list control group. PRIMARY comprises 28 consecutive days of questionnaires five times each day (i.e., ESM) and four weekly report sessions. Participants will comprise 180 young people referred for treatment to the participating Dutch mental healthcare institutions and (1) are aged 12 to 25 years, and (2) engaged in ≥ 1 act of self-harm in the past year. Participants are randomly allocated to a study group after screening in a 1:1 ratio by an independent researcher using computer-generated randomization sequences with stratified block randomization by age (12 to 15 years / 16 to 25 years). Staff will conduct assessments with all participants at baseline (Wave 1), after 28 days (Wave 2), and in a subsample after 10 weeks of subsequent specialized treatment (Wave 3). The primary outcomes are self-harm, emotion regulation, and quality of relationships. Secondary outcomes include patient and clinician satisfaction. Exploratory analyses of ESM data will examine the relationship between emotions, social relationships, and self-harm.

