### Measures

All study measures and their timing during the study are depicted in Table 1. All participants, independent of study group, fill out questionnaires at baseline (Wave 1) prior to commencing the study intervention, and at the end of the intervention phase (i.e., four weeks later; Wave 2). Participants who subsequently enroll in HYPE also fill out the questionnaires 10 weeks after starting their treatment (Wave 3). All assessments other than the ESM-questionnaire are administered to both the intervention and comparison group at the mental healthcare institution or through a video call with an RA, depending on the preferences of the participant.

**Table 1 Tab1:** Schedule of outcome measures

Construct	Measure	Screening	Wave 1	Intervention Phase	Wave 2	Wave 3
ESM-questionnaire*	Developed for study			X		

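### Allocation appears to precede the Wave 1 baseline, with staff unblinded and no exception for that visit, leaving an avoidable but limited route for bias in the ANCOVA covariate

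*Protocol article*

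**What the plan says.** Three places in the protocol article deal with the timing of allocation.

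- Abstract, Methods: "Participants are randomly allocated to a study group after screening in a 1:1 ratio by an independent researcher".
- Randomization and group allocation: "Once eligibility is confirmed during screening, participants are randomly assigned to the intervention or the comparison group in a 1:1 ratio".
- Recruitment procedure, in the text below Fig. 1: "the baseline assessment (Wave 1) is scheduled with the RA, after which the young person is randomly assigned to a study group".

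On blinding, Randomization and group allocation says "Staff will not be blind to group allocation. Participants are blind to their allocated group during Wave 1 assessment". It adds that the intervention makes concealment from participants and staff impossible.

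The abstract has staff conduct the assessments, and Measures places them "at the mental healthcare institution or through a video call with an RA". Data management says that participants enter their own answers in RoQua. Under Intervention group, PRIMARY starts only after Wave 1. The data analysis plan compares Waves 1 and 2 by group with ANCOVA, using the pre-test as covariate.

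**The concern.** A baseline covariate is safest when it is recorded before anyone in contact with the participant knows the arm. Here the allocation seems to exist when Wave 1 takes place, and the people running Wave 1 belong to a group described as unblinded.

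Two things could follow. An assistant who knows the arm could affect how the questionnaires are introduced or explained, or could let the allocation slip. Or Wave 1 could be rescheduled or lost more readily in one arm than in the other, after randomisation and before any baseline exists. The first would distort the covariate. The second would make the analysed groups less comparable than randomisation made them.

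The reason given for not blinding staff does not reach this visit. Nothing in the intervention requires staff to know the arm until Wave 1 is finished.

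**Working it through.** **1. The order of events.** The abstract and the randomisation section both put allocation at the end of screening. The statement that participants are blind during Wave 1 points the same way, since there must be an allocation for them to be blind to. The recruitment sentence can be read in two ways:
- allocation follows the scheduling of Wave 1, giving screening, booking, allocation, Wave 1, which agrees with the other two places;
- allocation follows Wave 1 itself, which does not agree.

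The literal reading is the first. The sentence is therefore ambiguous, not a proven contradiction.

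**2. Who knows the arm at Wave 1.** Staff are not blind, no visit is excepted, and assistants run the visit. It follows that the assistant may know. The article does not say when the assistant is told.

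**3. Which outcomes are touched.** Table 1 marks DERS-18 and NRI-BSV at Waves 1 and 2. As printed, it marks the self-harm questions at Screening only, which is before allocation. Objectives, however, compares Wave 1 with Wave 2 for all three outcomes. The concern is clear for DERS-18 and NRI-BSV and unsettled for self-harm.

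**4. The plan's own sample size.** Assume a medium effect of d = 0.5, two-sided alpha 0.05 and power 0.80. A two-sample t-test then needs 64 per group. With an assumed pre-post correlation r = 0.5, the ANCOVA factor gives 64 × (1 − 0.5²) = 64 × 0.75 = 48 per group, the stated figure. The power footnotes are not shown, so d and r are assumptions that happen to reproduce it. The order of allocation and Wave 1 does not change this number.

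**5. Illustration of size.** Suppose one arm's baseline is shifted by s SD with Wave 2 unaffected. The adjusted difference is then biased by about r × s SD, in a direction that depends on the sign of the shift.
- r = 0.5, s = 0.1: 0.5 × 0.1 = 0.05 SD.
- r = 0.5, s = 0.2: 0.5 × 0.2 = 0.10 SD.

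Against an assumed target of 0.5 SD, these are 10% and 20%. With 48 per group the standard error is √(2 × 0.75 / 48) = 0.177 SD, and the two-sided type I error rises from 5% to about 5.9% and 8.7%. Over r = 0.3 to 0.7 and the same two shifts, the bias runs from 0.03 to 0.14 SD and the type I error from 5.3% to 16%. No value of s comes from the documents.

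**The case against.** The strongest reply is that the baseline is already well protected. Participants type their own answers into RoQua and do not know their group. An independent researcher makes the allocation, and no sentence says that the assistant has been told by Wave 1. These points stand, and they make the route narrow. They do not close it: accidental disclosure and selective rescheduling or loss do not depend on who enters the answers.

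A reader might also infer four stronger things that the documents do not support.

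- **That the article gives two contradictory orders.** The literal reading of the recruitment sentence agrees with the randomisation section, and the flow diagram is not available to settle it.
- **That everyone lost between allocation and Wave 1 leaves the analysis.** The modified intention-to-treat rule keeps anyone with a data point after baseline, and multiple imputation will be considered. A missing baseline does not by itself exclude a participant. Someone who also has no later data would be excluded.
- **That the baseline is biased by 0.1 to 0.2 SD.** Those shifts are chosen for illustration, and the calculation further supposes that Wave 2 is untouched.
- **That Wave 2 should be completed away from the assistant for the same reason.** By then intervention participants know their arm, so self-report bias would remain. Safety considerations also names research assessments as an occasion on which acute suicidality may be identified. The present point gives no ground for altering that visit.

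**Conclusion.** The concern holds in a limited form. As written, allocation most plausibly precedes Wave 1, and nothing stops the assistant who runs the baseline from knowing the arm. The covariate for at least DERS-18 and NRI-BSV is therefore open to an avoidable influence, and participants can be lost between allocation and baseline. That the assistant does know is an inference from the general statement about staff.

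The size is unknown. The 0.05 to 0.10 SD rests on assumed values of r and of the shift, and shows only that a small baseline distortion would not be negligible beside a medium effect. Nothing shows that any distortion has occurred. The point is worth acting on mainly because the remedy is simple and the stated reason for unblinding does not apply before Wave 1.

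**What to change.** For participants still to be enrolled, the independent researcher should make the allocation, or at least release it to staff, only after the participant has submitted Wave 1 in RoQua. Making it then is the better of the two, because no one can be randomised and then lost before baseline. Releasing it then still keeps arm knowledge out of the baseline visit. Age, the stratification factor, does not depend on Wave 1, so the randomisation scheme need not change.

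State that single order in the abstract, in Recruitment procedure and in Randomization and group allocation, and limit the statement on unblinded staff to the time after Wave 1.

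The cost is small but real. The change needs a protocol amendment, and arranging the intervention starts slightly later. The first participant was included in October 2021, so the trial would contain participants enrolled under two procedures. The report should say so and give, by arm, the number allocated under the existing procedure who did not complete Wave 1. The sample size is unaffected.

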### Study groups

#### Intervention group

After baseline assessment (Wave 1), the intervention group starts with the PRIMARY intervention. PRIMARY is an intervention consisting of two elements: ESM and weekly, one-on-one structured report sessions based on the individual’s ESM-answers. Participants fill out the ESM-questionnaire via their smartphone five times a day for 28 consecutive days (i.e., 4 weeks). Each ESM-questionnaire appears at random times within blocks of 2.5 h periods. Participants can choose a starting time for the first block between 06:00 AM and 12:00 PM. To encourage compliance with the ESM-questionnaire protocol, motivating text messages are sent once a week. In case compliance drops below 70% during the previous three days, participants receive an extra text message to stimulate respondence (maximum of once a week). If a participant allocated to the intervention group does not have a smartphone or internet on their smartphone, they can borrow a smartphone from the research staff. The internet on this smartphone is limited to accessing the ESM-questionnaire and therefore does not change the participant’s situation regarding social interactions.

The weekly report session encompasses a 15-minute video call (or appointment at the institution on request of the participant) with the RA over the course of the ESM-procedure (i.e., four times). During these sessions, the answers provided on the ESM-questionnaire over the past week are discussed in a structured, scripted way using a graphical report in which the outcomes are summarized. These sessions aim to enhance the participant’s insight into the connection between their emotions, activities and social context.

#### Comparison group

After baseline assessment (Wave 1), participants in the comparison group receive care-as-usual, which entails a waiting list for further care.

### HYPE

After finishing the assessment at the end of the study intervention phase (i.e. Wave 2), it is anticipated that participants in an early stage of BPD (i.e., ≥ three BPD criteria) will receive specialized treatment called HYPE (Helping Young People Early) [41]. Allocation to HYPE is determined by clinicians independent from the study. HYPE is a time-limited integrative treatment program based on the principles of Cognitive Analytic Therapy (CAT). The time-limit comprises 16 individual, weekly psychotherapy sessions, supplemented with psychiatric, psychosocial and family sessions if indicated. There is a follow-up period of six months, wherein the young person can schedule up to four sessions.

### Measures

All study measures and their timing during the study are depicted in Table 1. All participants, independent of study group, fill out questionnaires at baseline (Wave 1) prior to commencing the study intervention, and at the end of the intervention phase (i.e., four weeks later; Wave 2). Participants who subsequently enroll in HYPE also fill out the questionnaires 10 weeks after starting their treatment (Wave 3). All assessments other than the ESM-questionnaire are administered to both the intervention and comparison group at the mental healthcare institution or through a video call with an RA, depending on the preferences of the participant.

**Table 1 Tab1:** Schedule of outcome measures

Construct	Measure	Screening	Wave 1	Intervention Phase	Wave 2	Wave 3
ESM-questionnaire*	Developed for study			X		
***Main study parameters***						
Self-harming thoughts and behaviors	Developed for study	X				
Emotion regulation	DERS-18		X		X	X
Quality of relationships	NRI-BSV		X		X	X

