### Objectives

The first objective of this RCT is to determine whether PRIMARY, compared to a waiting list control, is effective in improving the following outcomes: self-harm, emotion regulation, and quality of relationships. To this end scores at baseline (Wave 1) and at the end of the intervention phase (Wave 2) will be compared. The second objective is to examine the effectiveness of PRIMARY combined with subsequent specialized treatment in the early intervention program Helping Young People Early (HYPE) [41] in improving the outcomes for young people with borderline personality pathology. Scores on the specified outcome variables after 10 weeks of HYPE treatment (Wave 3) will be compared to scores at baseline (Wave 1) and at the end of the intervention phase (Wave 2) for participants who attended HYPE. The third objective is to investigate the associations between emotions, relational support and conflict, adaptive coping strategies, and self-harm using individual-level ESM data. The fourth objective is to examine the participants’ and clinicians’ satisfaction regarding the use of PRIMARY. This will be examined at the end of the intervention phase (Wave 2).

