***Other parameters***						
Demographics	Developed for study		X			
Concomitant treatment	Developed for study		X		X	X
BPD symptoms	SCID-II BPD PQ	X				
BPD behavior	BSL-23		X		X	X
Achievement of developmental milestones	DML		X		X	X
Life experiences	Modified LES		X		X	
Psychopathology	SPSY		X		X	X
Alternative Model for Personality Disorders	LPFS-BF PID-5-BF		X		X	X
Impulsivity	S-UPPS		X			
Internalizing problems	DASS		X		X	X
Loneliness	De Jong Gierveld questionnaire		X		X	X
Motivation for change	MYTS		X		X	X
Quality of life	ReQoL		X		X	X
Impact of COVID-19	Developed for study		X		X	X

**Only filled out by participants in the intervention group*

ESM = Experience Sampling Method, DERS-18 = Difficulties in Emotion Regulation Scale, NRI-BSV = Network of Relationships Inventory – Behavior Systems Version, UMUX = Usability Metric for User Experience, CSQ = Client Satisfaction Questionnaire, SCID-II BPD PQ = BPD section of the Structured Clinical Interview for DSM-IV Axis II disorders Personality Questionnaire, BSL-23 = Borderline Symptom List, DML = Developmental Milestones List, LES = Life Experiences Survey; SPSY = Screeningsinstrument Psychische Stoornissen, LPFS-BF = Levels of Personality Functioning Scale 2.0 Brief Form, PID-5-BF = Personality Inventory for DSM-5 Brief Form, S-UPPS = UPPS-P impulsive behavior scale short version, DASS = Depression Anxiety Stress Scales, MYTS = Motivation for Youth Treatment Scale, ReQoL = Recovering Quality of Life

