### Data analysis plan and power calculations

Analyses that cover effectiveness of PRIMARY will be performed according to a modified version of the *intention-to-treat* principle [71], which entails including all participants with at least one data point post-baseline regardless of their compliance during the study. This way, random selection in the sample will be guaranteed which ensures the most accurate conclusions following the analyses. In the following section, analyses will be outlined for each study objective (i.e., research question) as well as the required sample size to answer the research questions based on relevant power analyses and recent literature^1^. Multiple imputation will be considered if the amount of missing values is non-trivial. The randomization stratification variable of age and gender will be examined as covariates in the analyses described below. Other covariates, such as concomitant treatment, will also be considered.

To examine the effectiveness of PRIMARY, an ANCOVA-test will be used to compare data from Wave 1 and 2 by study group (study objective 1). Specifically, the following variables will be examined: emotion regulation, quality of relationships, and self-harm. To reach a power of 0.80, the power analyses run in G*Power 3.1 [72]^2^ and R [73], with an additional correction for the pre-test as a covariate, indicated a sample size of *n* = 48 per group to be necessary to detect a medium effect size (α = 0.05). Taking into account a drop-out of 10% (based on the feasibility study), a total sample size of *N* = 106 is necessary to answer this research question.

Regarding the effect of PRIMARY on the effectiveness of subsequent specialized treatment (i.e., HYPE), an ANOVA-test repeated measures with a within-between interaction will be applied to Wave 1, 2 and 3 including only those participants receiving HYPE treatment (study objective 2). To reach a power of 0.80, a sample size of *N* = 42-106 is necessary when considering a medium-large effect size (G*Power 3.1) [72]^1^. Taking into account the 10% drop-out from the feasibility study, a sample size of *N* = 46-118 is required (i.e., young people receiving HYPE treatment).

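### Table 1 schedules the self-harm questions at Screening only, although self-harm is a primary outcome to be compared between arms at Waves 1 and 2

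*Protocol article*

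**What the plan says.** The Abstract (Methods) states: "The primary outcomes are self-harm, emotion regulation, and quality of relationships". Under Objectives, the first objective is effectiveness on these three outcomes, for which "scores at baseline (Wave 1) and at the end of the intervention phase (Wave 2) will be compared". The second objective extends the same outcomes to Wave 3, ten weeks into HYPE, for participants who receive that treatment.

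The section on data analysis and power turns objective 1 into a model: "an ANCOVA-test will be used to compare data from Wave 1 and 2 by study group". It names the dependent variables: "the following variables will be examined: emotion regulation, quality of relationships, and self-harm".

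On timing, the Measures section says: "All study measures and their timing during the study are depicted in Table 1". In that table, under the main study parameters, the row "Self-harming thoughts and behaviors" (an instrument developed for the study) has one mark, under Screening. The text on main study parameters adds that there are five questions on frequency and severity, held in the supplement, and gives no assessment times. A further self-harm item sits in the ESM questionnaire. The Table 1 footnote says of the ESM questionnaire: "Only filled out by participants in the intervention group".

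**The concern.** An ANCOVA of Wave 2 on study group, adjusted for a pre-test, needs a Wave 2 value in both arms. For self-harm the published schedule provides none. The one post-baseline item that bears the name is collected in the intervention arm only, so it cannot support a comparison between arms.

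Reducing self-harm is the stated purpose of the intervention, and eligibility rests on it. If sites work from Table 1 as printed, the trial could report on emotion regulation and relationships but not on self-harm. Recruitment began in October 2021 and data collection is predicted to run until April 2026. A Wave 2 assessment that has been missed cannot be recovered later.

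**Working it through.** This is a check of the schedule against the objectives and the analysis.

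**Step 1. Read the rows of Table 1 by column.** The table has seven columns: construct, measure, Screening, Wave 1, Intervention Phase, Wave 2, Wave 3. The self-harm row has seven cells, so each cell falls under a definite column.

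| Measure | Screening | Wave 1 | Intervention Phase | Wave 2 | Wave 3 |
|---|---|---|---|---|---|
| Self-harm, five questions | X | – | – | – | – |
| DERS-18 (emotion regulation) | – | X | – | X | X |
| NRI-BSV (relationships) | – | X | – | X | X |
| ESM questionnaire (intervention arm only) | – | – | X | – | – |
| SCID-II BPD PQ | X | – | – | – | – |

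The neighbouring rows fall in sensible columns, and the other screening-only instrument reads in the same way. A fault in reading the table is therefore unlikely.

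**Step 2. Compare what the analyses need with what is scheduled for self-harm.**

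| Analysis | Needs | Scheduled on the five questions |
|---|---|---|
| Objective 1, ANCOVA by arm | pre-test and Wave 2, both arms | Screening only |
| Objective 2, repeated-measures ANOVA in the HYPE subset | Waves 1, 2 and 3 | none of the three |

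Screening precedes randomization, so a screening value could serve as the pre-test. It cannot serve as the outcome.

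**Step 3. Look for another place that repairs the schedule.**

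- The Measures section says that all participants complete questionnaires at Waves 1 and 2, and that everything except the ESM questionnaire is given to both arms. It does not name the self-harm questions, and it refers to Table 1 for timing. It cannot mean every instrument at every wave, because Table 1 marks S-UPPS at Wave 1 only and SCID-II BPD PQ at Screening only.
- The description of the five questions gives no timing.
- The ESM item covers the intervention arm only.

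None of these schedules the five questions at Wave 2.

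**Step 4. Check that the sample size presupposes both values.** The plan states 48 per group for a medium effect, power 0.80, α = 0.05, with a correction for the pre-test. Assuming d = 0.5 and a two-sided test, the two-sample t-test needs 64 per group. With an assumed pre-post correlation r, the correction is n × (1 − r²):

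- r = 0.5: 64 × (1 − 0.25) = 48, the plan's figure.
- r = 0.3: 64 × 0.91 = 58.2, so 59.
- r = 0.7: 64 × 0.51 = 32.6, so 33.

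For drop-out, 96 × 1.1 = 105.6, which rounds up to the stated 106 (96 / 0.9 = 106.7, so 107). The figure therefore reproduces with r = 0.5. It rests on a pre-test and a Wave 2 value for each outcome, and Table 1 does not schedule a Wave 2 value for self-harm.

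**The case against.** The strongest reply is that this is an omission in the table. The abstract, the objectives and the analysis plan all treat self-harm as measured at Waves 1 and 2, and the Measures section says in general terms that both arms complete questionnaires at those waves. Marks dropped from one row are at least as plausible as a trial that does not collect a primary outcome. This stands as a limit on the claim. It does not remove the contradiction, because the table is offered as the complete schedule and a reader cannot tell which version the sites follow.

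Four stronger readings are tempting, and the documents do not support them:

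- A reader might infer that the whole comparison arm lacks the outcome at Wave 2. That holds only if the printed schedule is the one in use, which the document does not settle.
- A reader might call self-harm the lead outcome. It comes first in the abstract and last in the analysis section, and no hierarchy is stated.
- A reader might carry the past-year eligibility window over to Wave 2 and conclude that the effect would be heavily diluted. The recall period of the five questions is in a supplement that is not shown, and nothing says that the eligibility window is reused.
- A reader might propose the BSL-23 behavior scale, collected at Waves 1 to 3, as a substitute. The article labels it as BPD behavior under other parameters and does not say that it measures self-harm.

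**Conclusion.** The contradiction is real and concerns a primary outcome. Under the schedule as printed, the number of Wave 2 values on the designated self-harm measure is zero in both arms. In the comparison arm there is also no post-randomization value from either source named as self-harm. Objective 1 could then not be answered for self-harm, and objective 2 would lack it at all three waves. The blank at Wave 1 matters less than the blank at Wave 2, because the screening value could stand in as the pre-test.

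The conclusion rests on Table 1 being the complete schedule, as the Measures section says, and on the row being printed as intended. If the second assumption fails, the error is confined to the table. The planned analysis then has its data, but the published protocol is still wrong on when a primary outcome is measured.

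**What to change.** Reconcile Table 1 with the Objectives and with the data analysis section, and state in the text when each arm completes the five self-harm questions.

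- If they are already given at Waves 1, 2 and 3, add the marks to Table 1. The cost is a correction to one row.
- If they are not, amend the schedule so that both arms complete them at Wave 1 and Wave 2, and the HYPE subset at Wave 3. Use the same recall period at each wave, no longer than the four weeks between Waves 1 and 2, so that the Wave 2 answer does not reach back before the intervention phase. Report, by arm, how many participants passed Wave 2 without the measure. The cost is a schedule amendment and five short items in assessments that both arms already attend. Values already missed cannot be recovered, so the amendment should be made promptly.
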